### Interventions

The intervention treatment period includes 12 sessions over 6 weeks. The participants will visit the research center twice a week through the 6 week period. Licensed Korean medical doctors who have at least 1 year of clinical experience will perform the intervention. Detailed information regarding the schedule of the enrolment, interventions, and assessments is provided in Additional file 1 and Table 1.

For the EA and AC groups, disposable, sterilized, filiform needles (diameter 0.25 mm, length 40 mm; Dong-Bang Acupuncture Inc., Seoul, Korea) will be inserted into the skin at the following acupoints: unilaterally at CV3, CV4, and GV20, bilaterally at KI3 and SP6. When inserting at CV3, the needling direction will be toward CV2. The needles will be inserted to a depth of between 5 and 30 mm, and the acupuncture needles will be manipulated to achieve de qi and retained for 20 min.

In the EA group, electrical stimulation will be performed simultaneously during the retaining period. An electric acupuncture device (CellMac STN-110, Stratek Co., Republic of Korea) will be connected to the CV3-CV4 and KI3-SP6 acupoints and deliver stimulation with a 2 Hz frequency, asymmetric bimodal pulse, continuous wave mode, and a maximum intensity below the threshold (7.6–13.9 mA). Electrical stimulation will be delivered at an intensity that the participant can notice but will still feel comfortable with.

### Prohibited and permitted concomitant treatment

Participants will be prohibited from receiving any OAB treatment outside of the interventions of this trial during the 6-week treatment period. If a patient start medication for OAB during the treatment period, they will be withdrawn from the trial. All new treatments started after the beginning of the trial and concomitant medications to treat medical conditions unrelated to OAB will be recorded on the Case Report Form (CRF).

### Outcomes

Although it is impossible to ensure blinding for intervention conductor and the participants, we will ensure blinding for the outcome measurements analyses by independent assessors unaware of group allocation. The following outcomes will be assessed by independent assessors blinded to the allocation. Efficacy will be assessed by the 3-day bladder diary, the OABSS and the KHQ.

#### Primary outcome

The primary outcome measurement of this study is the average number of micturitions per 24 h based on the 3-day bladder diary at the end of the treatment period (week 6).

Participants will complete a 3-day bladder diary before and after treatment (week 6), and the follow-up period (week 10). Entries will be recorded in micturition diaries for 3 days before each follow up visit. Participants will record the time of every micturition and rate the intensity of urgency using the five-point URS (1 = no urgency, 2 = mild urgency, 3 = moderate urgency, 4 = severe urgency, 5 = UUI).

#### Secondary outcome

Secondary outcome measurements will include the number of micturitions in the 3-day bladder diary at the end of the treatment period (week 6) and the follow-up period (week 10). The same version of the 3-day bladder diary will be applied again. This includes daytime micturitions per 24 h, nocturnal micturitions per 24 h, total count of urgency (sum of urgency episodes defined as URS ≥ 3 for three days), total urgency score (sum of urgency score for three days), and total count of UUI (sum of UUI episodes for three days).

In addition, the OABSS and the KHQ will be measured as secondary outcomes. Participants will complete the Korean version of the OABSS and the KHQ at baseline, the end of the treatment period (week 6), and the follow-up period (week 10).

The OABSS is an assessment tool for OAB symptoms that was developed and validated in Japanese populations in 2006 [16]. The OABSS consists of four questions regarding OAB symptoms; daytime frequency, nocturia, urgency, and UUI. The sum of the four scores runs between 0 and 15. The diagnostic criteria for OAB is a total OABSS of ≥3 with an urgency score for question 3 of ≥2 [17].

The KHQ is an assessment tool for quality of life data of OAB symptoms that was developed by Kelleher and colleagues [18, 19]. The KHQ is a urine questionnaire that can assess the severity of urination symptoms and evaluate the impact of urination symptoms on quality of life. This questionnaire is known to have reliability and validity for measuring the quality of life of patients with incontinence [20]. The 10 domains from the KHQ evaluated are general health perception, incontinence impact, role limitations, physical limitations, social limitations, personal relationships, emotions, sleep/energy, severity measures, and symptom severity.

### Safety assessment

All participants will be monitored for adverse events during the study. Adverse events (AEs) indicate undesirable and unintentional signs, symptoms, or diseases that develop after intervention during the period of a clinical trial. They do not necessarily have a causal relationship with the relevant intervention. Investigators will check participants’ vital signs and examine for manifestation of AEs at each visit. Investigators will also conduct physical examinations and laboratory tests, including evaluation of urinalysis (specific gravity, nitrite, pH, protein, glucose, ketones, urobilinogen, bilirubin, blood, white blood cells, urine HCG) at the screening as well as at the end of treatment period (week 6). The outcome assessors will judge the severity (none, mild, moderate, or severe), seriousness, and the correlation between AEs and intervention (definitely related, appears to be related, possibly related, appears to be unrelated, definitely not related, or unclear).

### Sample size

The primary outcome of this study will be the average number of micturitions per 24 h after the treatment. Based on a previous study [21], we estimated that the mean difference in the pre- and post-treatment change in the average number of micturitions per 24 h scores between the EA and AC group will be 0.8 and the standard deviation will be 2.1. With a 5% significance level and 80% power, the needed sample size was calculated to be 116 per group. Considering a 20% drop-out rate, 145 participants are required per group. In conclusion, a total of 290 participants are needed in this trial.

### Statistical analysis

We will analyze results primarily based on the principle of intention-to-treat (ITT) and subordinately based on the per-protocol (PP) principle. The ITT analysis will include any participants who are randomly allocated and have at least one EA or AC session. The PP analysis will cover only patients who have completed at least 10 sessions of EA or AC treatments with no use of medication or medical device of UTI or OAB, and have no serious violation. The primary and secondary continuous outcomes will be compared between randomized groups using ANCOVA models that includes baseline measurement as covariates.

The categorical variables will be analyzed by the Pearson χ^2^ test or Fisher’s exact test. If there is a significant difference between groups in terms of baseline characteristics, analysis of covariance (ANCOVA) or logistic regression for further evaluation will be performed. When it is necessary to control important variables that may affect the final evaluation, stratification analysis (Cochran-Mantel-Haenszel method, etc.) will be applied.

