**Methods/design:**

This is a multicenter, randomized controlled, parallel clinical trial. Two hundred ninety participants with overactive bladder syndrome will be recruited from Dongguk University Bundang Oriental Hospital and Cheonan Korean Medicine Hospital of Daejeon University and randomly allocated into one of two groups in a 1:1 ratio. One group will receive electroacupuncture (EA) and the other acupuncture (AC). The allocation will be concealed from both participants and assessors. The study period will be about 10 weeks, including 6 weeks of electroacupuncture or acupuncture treatment and a four week follow-up period. Both EA group and AT group will undergo acupuncture at 7 fixed points, and the EA group will undergo electronic stimulation at 6 points. The primary outcome will be the average number of micturitions per 24 h based on a 3-day bladder diary. The secondary outcome will comprise the 3-day bladder diary, the overactive bladder symptom score and the results of the King’s health questionnaire.

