### Randomization, allocation concealment and blinding

A table of random numbers will be produced according to sample size using the statistical software SAS (version 9.4; SAS Institute Inc., Cary, NC, USA), and sealed in opaque envelopes. The envelopes will be delivered to each research center and stored in a double-locked cabinet. The practitioner will open the corresponding envelope and allocate the participants who meet the eligibility criteria after signing an informed consent form. Participants will be randomly allocated to the electroacupuncture (EA) group or the acupuncture (AC) group at a ratio of 1:1. After the practitioner checks the group allocation for the subject, the envelope will be stored again in a separate, double-locked cabinet.

Randomization will be stratified by centers and is conducted with concealment of the randomization list.

Practitioners cannot be blinded, and they will be excluded from the assessment procedure. Outcomes will be assessed by researchers who are not involved in the intervention procedure.

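### The primary set called ITT leaves out randomised women who receive no session, although the practitioner knows the arm before session 1; the likely bias is small

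*Protocol article*

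**What the plan says.** All references are to the protocol article.

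- **Statistical analysis** ranks the analyses: "We will analyze results primarily based on the principle of intention-to-treat (ITT) and subordinately based on the per-protocol (PP) principle". It then defines the first set: "The ITT analysis will include any participants who are randomly allocated and have at least one EA or AC session". The only other set is per-protocol, which is narrower (at least 10 sessions, no disallowed treatment, no serious violation).
- **Randomization, allocation concealment and blinding** says who learns the arm, and when: "The practitioner will open the corresponding envelope and allocate the participants who meet the eligibility criteria after signing an informed consent form". It adds: "Practitioners cannot be blinded, and they will be excluded from the assessment procedure".
- **Outcomes** says that "it is impossible to ensure blinding for intervention conductor and the participants", whereas the **Abstract** (Methods/design) says: "The allocation will be concealed from both participants and assessors".
- **Table 1** (Study design) marks random allocation and the first acupuncture treatment at Visit 2. The baseline 3-day diary is also marked there.
- **Dropout criteria** removes from the study any woman who fails, or expects to fail, to attend 10 sessions.

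**The concern.** Intention-to-treat protects the comparison because membership of the analysis set is settled at randomisation. Here membership also needs an event after randomisation, namely receipt of a first session. Such a rule is usually harmless when nobody who can influence that event knows the arm. That condition is not met: the practitioner has read the allocation before deciding to proceed with session 1, and must know it in order to connect or not connect the current.

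If women who drop out at that point differ in number or prognosis between arms, the primary comparison is no longer fully protected by randomisation. Even if none are lost, the result would be reported as ITT when the set is a treated one.

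**Working it through.** **Step 1. Is the exclusion real?** The definition has two conditions joined by *and*: randomised, and at least one session. A woman who meets only the first is excluded. The per-protocol set does not bring her back, and no third set is described.

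**Step 2. Who knows the arm before session 1?**

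| Person | Source | Knows before session 1? |
|---|---|---|
| Practitioner | Randomization section: opens the envelope, not blinded | Yes |
| Participant | Abstract: concealed. Outcomes: blinding cannot be ensured | Unclear; the two must be reconciled |
| Assessor | Abstract and Outcomes: blinded | No |

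The practitioner's knowledge alone is enough for exclusion to be able to depend on the arm.

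**Step 3. How long is the window?** The Interventions section gives 12 sessions, and Table 1 marks treatment at Visits 2 to 13, which is 13 − 2 + 1 = 12 visits. So session 1 is at Visit 2, the visit at which allocation is marked. The window lies within one visit.

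**Step 4. How large could the shift be?** The document gives no expected number of women without a session, so there is no plan figure to reproduce on this point. Inputs from the Sample size section are a difference of 0.8, an SD of 2.1, 116 evaluable women per arm and 145 randomised per arm (116 / 0.80 = 145, which reproduces).

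Assumptions, not taken from the document: a fraction q of one arm only is excluded, with q = 1% to 5% (0.01 × 145 = 1.45 and 0.05 × 145 = 7.25, so about 1 to 7 women). Excluded women differ from the retained women of that arm by D = 0.5 to 1 SD, that is 0.5 × 2.1 = 1.05 to 2.1 micturitions per 24 h.

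Full-arm mean = (1 − q) × retained mean + q × excluded mean = retained mean + q × D. Dropping the excluded women therefore shifts the arm mean by q × D.

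To express this as type I error, take a true effect of 0, 116 per arm and a two-sided 5% test. The standard error is 2.1 × √(2/116) = 0.276. With b = q × D / 0.276, the rejection probability is P(Z > 1.96 − b) + P(Z < −1.96 − b).

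| q | D | Shift q × D | Share of 0.8 | Two-sided type I error |
|---|---|---|---|---|
| 1% | 1.05 | 0.011 | 1.3% | 5.0% |
| 1% | 2.1 | 0.021 | 2.6% | 5.1% |
| 5% | 1.05 | 0.053 | 6.6% | 5.4% |
| 5% | 2.1 | 0.105 | 13.1% | 6.7% |

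These figures are before baseline adjustment. The planned ANCOVA would remove the part of D explained by baseline frequency. Losses in both arms with the same q and D would cancel in the difference.

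**The case against.** The strongest defence is that almost nobody can fall into the gap. Allocation and first treatment share a visit, the woman has come to be treated, and both arms receive the same needling. The envelope is opened only for women who are already eligible and have consented. None of the stated grounds for leaving (unwillingness, missing sessions, starting OAB medication) is a practitioner's preference. The definition is also printed openly, so a careful reader can see what the set is. All of this stands as an argument about size. It does not make the rule independent of the arm, nor the label accurate.

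Two stronger readings are tempting and are not supported.

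- *Women learn their arm, dislike it and leave before session 1.* No section says a woman is told her arm. The Abstract says the opposite, and the Outcomes section says only that blinding cannot be ensured. If she infers her arm from the presence or absence of current, she does so during session 1, when she already counts in the set.
- *The primary result will be materially biased.* The loss fractions and gaps are assumed, and all loss is put in one arm. Striking figures need extreme inputs: a type I error of 33% requires 10% of one arm lost (about 14 to 15 women) and a 2 SD gap (0.10 × 4.2 = 0.42). Nothing in the document points to losses of that order within one visit.

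A further objection stands and shapes the remedy. The Dropout criteria would remove a woman with no session from the study whatever the ITT sentence says. Rewording that sentence alone would turn her from an exclusion into a missing value.

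**Conclusion.** The point holds in a limited form. The primary set is a modified (treated) set carrying the ITT label. Membership depends on an event after randomisation, and the practitioner knows the arm when that event is decided. No all-randomised analysis is described beside it. Participants' knowledge of their arm is unresolved in the document, and the conclusion does not rest on it.

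The expected effect is small: 0.01 to 0.11 micturitions per 24 h, or 1% to 13% of the planned 0.8. This assumes one-arm losses of 1% to 5% and a gap of 0.5 to 1 SD, before baseline adjustment. The upper end is hard to square with same-visit treatment. The case for change is that the definition is inaccurate and cheap to correct, not that serious bias has been shown.

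**What to change.** 1. In Statistical analysis, define the primary ITT set as all randomised women, analysed in the arm assigned, whatever the number of sessions received.
2. Keep the set requiring at least one session under another name, for sensitivity or safety, and report the number of women without a session by arm.
3. Reconcile the Dropout criteria with this definition, so that missing sessions does not end outcome collection and the week-6 and week-10 diaries are still requested. This is feasible: the diary is self-recorded, and the baseline diary is scheduled at the allocation visit, so the ANCOVA covariate should be available.
4. Reconcile the Abstract and the Outcomes section on whether participants are blinded.

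The cost is a few sentences of wording and diary requests to what should be a handful of women. Some of those diaries will not come back, so the analysis gains a few missing values, and including untreated women may slightly dilute the estimated effect.

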### Eligibility criteria

Two hundred ninety patients with OAB will be recruited from two hospitals in Korea: Dongguk University Bundang Oriental Hospital in Bundang, and Cheonan Korean Medicine Hospital of Daejeon University in Cheonan. After obtaining informed consent from the patients or their representatives, we will screen them according to the eligibility criteria for enrollment in the study.

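### Randomisation is stratified by centre, but the stated ANCOVA names only the baseline value as covariate, so precision is lost if the two centres differ

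*Protocol article*

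**What the plan says.** Under Eligibility criteria the protocol article states that "Two hundred ninety patients with OAB will be recruited from two hospitals in Korea". Under Randomization, allocation concealment and blinding it states that "Randomization will be stratified by centers and is conducted with concealment of the randomization list". Centre is therefore the one stratification factor, with two levels. That section mentions a table of random numbers and a 1:1 ratio, but no blocks.

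Under Statistical analysis the model is described as follows: "The primary and secondary continuous outcomes will be compared between randomized groups using ANCOVA models that includes baseline measurement as covariates". Two further clauses there deal with adjustment:

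- The first provides for a further ANCOVA or logistic regression if the arms turn out to differ significantly at baseline.
- The second reads: "When it is necessary to control important variables that may affect the final evaluation, stratification analysis (Cochran-Mantel-Haenszel method, etc.) will be applied".

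Neither clause names centre, and both are conditional.

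**The concern.** A factor that restricts the randomisation normally belongs in the model. If arms are balanced within centre, a difference in level between the hospitals does not disturb the treatment contrast, yet a model without centre counts it as residual error. The interval is then wider than it need be and power is lost.

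The two conditional clauses do not repair this. The first is triggered by a significant baseline imbalance between arms, and the better the stratification works, the less likely centre is to show one. The second applies when judged necessary, names no variable, and gives as its example a method for categorical data, whereas the primary outcome is a mean count analysed by ANCOVA.

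What is at stake is efficiency: the trial stratifies by centre and may then not collect the precision that this offers.

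**Working it through.** **Inputs.** From Sample size: a between-arm difference in change of 0.8 and an SD of 2.1; the statement "With a 5% significance level and 80% power, the needed sample size was calculated to be 116 per group"; and an allowance of 20% for dropout, which leads to 145 per arm. The article does not say whether the test is one- or two-sided; two-sided is assumed here.

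**The plan's own figure.** n per arm = 2 × 2.1² × (1.960 + 0.842)² / 0.8² = 108.2, hence 109 (110 with the t distribution). The stated 116 does not follow exactly from these inputs, but it errs on the safe side. From 116 the rest does follow: 116 / 0.80 = 145 per arm, 290 in total. With 116 evaluable per arm:

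- SE = 2.1 × √(2/116) = 0.276
- power = Φ(0.8/0.276 − 1.960) = 82.7%

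This is the reference for a model that includes centre, taking 2.1 as the within-centre residual SD.

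**Leaving centre out.** Let D be the centre difference in micturitions per 24 h that remains after baseline adjustment. D is an assumption. With two equal centres the between-centre variance is 0.25·D², so:

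- reported SE = 0.276 × √(1 + 0.25·D²/2.1²)
- arms balanced within centre: the true SE stays 0.276, so power = Φ((0.8 − 1.960 × reported SE)/0.276) and true alpha = 2 × [1 − Φ(1.960 × reported SE/0.276)]
- unblocked: the reported SE is the true SE, so alpha is 5% and power = Φ(0.8/reported SE − 1.960)

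| D | SE without centre | Increase | Power, balanced | True alpha, balanced | Power, unblocked |
|---|---|---|---|---|---|
| 0 | 0.276 | 0% | 82.7% | 5.0% | 82.7% |
| 0.5 | 0.278 | 0.7% | 82.3% | 4.8% | 82.1% |
| 1.0 | 0.283 | 2.8% | 81.2% | 4.4% | 80.6% |
| 1.5 | 0.293 | 6.2% | 79.4% | 3.7% | 78.0% |
| 2.0 | 0.305 | 10.8% | 76.7% | 3.0% | 74.5% |

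Example at D = 2: √(1 + 1/4.41) = 1.108. With a 70:30 split between centres the loss is slightly smaller (power 77.7% at D = 2, balanced).

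**Simulation check** (232 evaluable, 5,000 runs per scenario, ANCOVA with and without centre, D = 2):

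- Blocks of 4 within centre: mean reported SE 0.306 against a true SE of 0.278; power 75.5% without centre and 81.5% with it; type I error 2.9% without centre.
- No blocks: mean reported SE 0.306 against a true SE of 0.305; power 73.5% without centre and 81.9% with it; type I error 5.3% without centre, within simulation error of 5% (√(0.05 × 0.95/5000) = 0.3 points).

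The loss of 6.0 points under blocking equals the analytic loss (82.7 − 76.7).

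**If 2.1 is a total SD that already contains centre variation.** At D = 2 the within-centre SD is √(4.41 − 1) = 1.85. Under balance, power is 85.8% without centre and 91.0% with it. Planned power is kept, and the cost is a gain not taken.

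**The case against.** The strongest reply is that the article is a condensed account. Its sentence says that the models include the baseline measurement; it does not say that they contain nothing else, and a statistical analysis plan that is not shown may add centre. This stands as far as it goes: a reader might infer that the plan rules centre out, and the wording does not support that. It remains true that the article names the covariate for the primary and continuous secondary outcomes and leaves out its own design factor.

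Second, a reader might infer that the standard error is necessarily wrong for this design and the test necessarily conservative. That needs balance within centre, as blocks would give, and no blocking is stated. Without it the baseline-only standard error is valid. This objection stands in full and confines the alpha figures to the blocked case.

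Third, the size rests on an undocumented D. Values of 1.0 to 2.0 are 1.25 to 2.5 times the expected treatment effect of 0.8, and they must survive baseline adjustment in centres that share entry criteria and a treatment protocol. At D = 1.0 power still exceeds 80%. It is also tempting to say that the hospitals use different practitioners. That is a plausible inference, but the article gives only a common qualification for them.

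Fourth, 2.1 is given for the pre-to-post change and comes from a previous study. It may already include centre variation, in which case planned power is not at risk.

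**Conclusion.** The point holds as a modest matter of efficiency. The stated ANCOVA does not name the factor by which the trial randomises, and nothing else in the section reliably brings it in.

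With 116 per arm, equal centres and a within-centre SD of 2.1, the loss of power at a centre difference of 1.0 is 1.5 points if arms are balanced within centre (82.7 − 81.2) and 2.1 points if allocation is unblocked (82.7 − 80.6). At 2.0 it is 6.0 and 8.2 points. It is nil if the centres do not differ.

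A reader might go on to infer a biased treatment estimate or too many false positives. Neither follows: the omission makes the test conservative under blocking and leaves it at its nominal level otherwise. In every scenario computed with a centre difference, the model with centre has the higher power.

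**What to change.** State the primary model as: week-6 outcome = arm + baseline value + centre (fixed effect). Use the same model for week 10 and for the continuous secondary outcomes. Centre should enter unconditionally, not through the clauses on baseline imbalance or necessity. If the full protocol or the statistical analysis plan already includes centre, it is enough to confirm this and align the published wording.

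The cost is one degree of freedom (229 to 228 with 232 evaluable participants). No new data are needed, and the change is worth making whether or not allocation is blocked.

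### Further adjusted and stratified analyses are triggered by baseline significance tests or an undefined need, are not ranked below the fixed ANCOVA, and centre is left out of the model

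*Protocol article*

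**What the plan says.** The Statistical analysis section of the protocol article contains three statements that bear on covariates.

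- Primary and secondary continuous outcomes are compared by ANCOVA with the baseline measurement as covariate. This is unconditional, and no other covariate is named.
- "If there is a significant difference between groups in terms of baseline characteristics", then ANCOVA or logistic regression is to be performed as a further evaluation. The variables to be tested and the level of the tests are not given.
- "When it is necessary to control important variables that may affect the final evaluation, stratification analysis" is to be applied, with Cochran-Mantel-Haenszel as one example and the list left open. There is no criterion for necessity, no variable and no timing.

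The section does not say which result decides if these analyses disagree. It does rank the analysis populations, with intention-to-treat first and per-protocol second, so the lack of a ranking for the models stands out.

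The Randomization section adds: "Randomization will be stratified by centers". Centre is therefore a design factor known in advance, but the ANCOVA does not include it.

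**The concern.** Participants are allocated at random to the "electroacupuncture (EA) group or the acupuncture (AC) group at a ratio of 1:1". Any baseline difference that reaches significance has then arisen by chance. Its p-value depends on the size of the chance imbalance and says nothing about whether the variable predicts micturition frequency. A rule based on that p-value can bring in irrelevant variables that happen to differ, and leave out prognostic ones that happen to balance.

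The second rule has no criterion at all. Between them, the two rules can produce several versions of the same treatment comparison, and nothing in the text says which one the conclusion rests on. At stake are the control of the 5% level if a choice between versions is made, the precision given up by not fixing useful covariates, and an analysis that does not reflect the stratified randomisation.

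**Working it through.** **Inputs.** From the Sample size section: "With a 5% significance level and 80% power"; a difference "between the EA and AC group will be 0.8 and the standard deviation will be 2.1"; "the needed sample size was calculated to be 116 per group"; and "Considering a 20% drop-out rate, 145 participants are required per group". A two-sided test is assumed, since sidedness is not stated. The number, independence and strength of the baseline variables are also assumptions, because the article gives none of them.

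**The plan's own figure.** n per group = 2 × [2.1 × (1.960 + 0.842) / 0.8]² = 108.2, so 109 (110 with the t distribution). The stated 116 is not reproduced but errs on the large side, and does not affect this point. The dropout step does reproduce: 116 / 0.80 = 145 per group, 290 in total. The checks below use 116 per group.

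**How often the trigger fires by luck.** With k independent tests at 5%, the chance of at least one significant result is 1 − 0.95^k.

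| k | Chance |
|---|---|
| 5 | 22.6% |
| 10 | 40.1% |
| 15 | 53.7% |
| 20 | 64.2% |

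**Type I error, several covariates.** This was simulated under no treatment effect: 116 per group, 10,000 runs per scenario, Monte Carlo standard error about 0.2 percentage points. Outcome-baseline correlation was 0.5, with 5 or 10 further covariates explaining 10%, 30% or 50% of the variance left after baseline.

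| Strategy | Type I error across six scenarios |
|---|---|
| Baseline-only ANCOVA, fixed | 4.4% to 5.2% |
| Trigger followed mechanically, its result decides | 3.3% to 4.8% |
| Better of base and triggered model | 5.0% to 5.7% |
| Free choice of the best among base, triggered, single-covariate and full models | 7.7% to 12.9% |

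**Type I error, one covariate.** Let the covariate have correlation r with the outcome.

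- *Free choice in every trial.* Under the null the unadjusted and adjusted statistics are bivariate normal with correlation √(1 − r²), which is 0.954 at r = 0.3 and 0.866 at r = 0.5. The chance that at least one exceeds 1.96 in absolute value is 6.4% and 7.3%.
- *Choice only when the baseline test fires.* Simulation (20,000 runs) gives 5.2% and 5.1%.
- *Rule followed mechanically.* The same simulation gives 4.8% and 4.2%.

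**Precision.** Power ≈ Φ(0.8 / [2.1 × √(1 − r²) × √(2/116)] − 1.96). Here r must be read as the correlation with what remains after baseline adjustment, and 2.1 as the SD of that remainder.

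| r | Residual SD | Power with fixed adjustment |
|---|---|---|
| 0 | 2.10 | 82.7% |
| 0.2 | 2.06 | 84.2% |
| 0.3 | 2.00 | 86.0% |
| 0.5 | 1.82 | 91.8% |

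A simulation at r = 0.5 (5,000 runs) gave 82.4% without the covariate, 83.3% with test-then-adjust and 91.5% with fixed adjustment. The trigger therefore recovers 0.9 of the 9.1 percentage points available. With a single covariate this is expected: the baseline test fires in only about 5% of trials, so the covariate is left out of the rest.

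**The case against.** The strongest reply is that the primary comparison is already fixed. The baseline-adjusted ANCOVA is stated without condition. The triggered models come in a separate paragraph that opens with categorical variables, they are described as further evaluation, and nothing says they replace the ANCOVA. This stands. A reader might infer that the primary model itself depends on the data and that its 5% level is lost; the article does not support that. What remains is that it never says the ANCOVA alone decides, and it speaks of variables affecting the final evaluation.

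A reader might also infer that the baseline-test rule by itself raises type I error to 6% to 8%. It does not. Applied as written it is slightly conservative, and even taking the better result when it fires adds little. The larger figures need an ungated choice that the baseline trigger does not allow. The necessity rule does not exclude such a choice, but it gives no timing, and its one named method is for categorical data, so its bearing on the primary outcome is limited.

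On power, a contrast of 82% with 92% would overstate the loss. The plan already adjusts for baseline, and no document names a further variable correlated 0.5 with the remainder. At r = 0.2 the gain is about 1.5 percentage points (84.2% − 82.7%).

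Finally, it can be said that covariate lists belong in an analysis plan. That is fair for detail left out. Here, however, the article states a selection method, and the method is poor.

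**Conclusion.** The point holds in a limited form. The base ANCOVA is sound and fixed. The faults are an arbitrary way of choosing further covariates, a set of extra analyses with no stated rank, and the omission of the one stratification factor.

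The trigger would fire by luck in about 40% of trials with 10 independent variables and about 64% with 20; both counts are assumed. Type I error is about 4% to 5% if the trigger is followed mechanically (as low as 3.3% when the covariates explain half the remaining variance). It is about 5% to 6% if the better of the base and triggered results is taken. It is about 6% to 7.5% if adjusted and unadjusted results can be chosen freely with one covariate correlated 0.3 to 0.5, and more only under freer choice among many models. The loss of precision is real in direction, but its size depends on covariate strength beyond baseline, which the article does not give. The change is worth making because it costs almost nothing, not because the primary test is shown to be invalid.

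**What to change.** 1. Delete the rule that adds adjusted models after a significant baseline difference, and the rule that adds stratified analyses when judged necessary.
2. Fix the model for the primary and other continuous outcomes as ANCOVA with the baseline value of the outcome and centre.
3. Apply the same principle to categorical outcomes: an analysis fixed in advance that accounts for centre.
4. State that this analysis alone decides for each outcome, and label every other adjusted or stratified analysis as sensitivity.

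Further prognostic covariates such as age or OABSS are optional and not part of the required change. OABSS has daytime frequency and nocturia items, so it overlaps with the baseline value already in the model.

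The cost is a few sentences of text, one degree of freedom for the two-centre term, and the analyst's freedom to choose models later. No new data are needed and the sample size does not change.
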